###### Combining the predictive models to form a draft tool

The three derived models will be combined to form a single, Excel-based draft version of a tool that seeks to provide estimates of an individual’s risk of death/recontact with the UEC system if managed by non-conveyance; risk of death/recontact with the UEC system if managed by conveyance; and the risk of their attendance at ED being classed as an AA if conveyed. The manner in which it is presented will be informed by WP1b and previous work by Bonnett *et al*.^86^ Examples of tools that have combined predictive models to provide clinicians with different estimates to inform decisions include the CHA2DS2-VASc/HAS-BLED^87^ and the cancer PREDICT tool.^88^

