### Current project

#### Overview and aims

To address the identified needs and information gaps, the 24-month mixed-methods RADOSS project is being completed. It has the following aims: (1) calculate the risks and benefits of conveyance to hospital after a suspected seizure; (2) create a risk prediction tool that predicts the likelihood that an individual will die and/or recontact the UEC system within 3 (and 30) days if not conveyed and the likelihood that their conveyance to ED would result in an AA; and (3) establish a pathway to clinical implementation of the risk prediction tool and maximise usage of RADOSS findings. The project’s related objectives were noted in table 1.

**Table 1 T1:** The RADOSS project’s aims and objectives and the work packages that address them

Aims	Objectives
(1) Calculate the risks and benefits of conveyance to hospital after a suspected seizure.	a. Describe the characteristics of those conveyed and those not conveyed to ED by one representative English ambulance service (WP1a).
	b. Compare the proportions following conveyance and non-conveyance that die and/or recontact the UEC within 3 (and 30) days (WP1a).
	c. Quantify the proportion of incidents conveyed to ED that meet the definition of an AA (WP1a).
(2) Create a risk prediction tool that predicts the likelihood that an individual will die and/or recontact the UEC system within 3 (and 30) days if not conveyed and the likelihood that their conveyance to ED would result in an AA.	d. Optimise the prediction tool development by completing KE workshops with service users and ambulance and ED clinicians to get views on predictors considered for inclusion in the models, the way the outcome measures of death, UEC recontact and AA are defined and risk score presentation (WP1b).
	e. Develop statistical models to predict a person’s risk of death/recontact with the UEC system within 3 (and 30) days and the likelihood of their attendance at ED being classed an AA if conveyed (WP1a).
	f. ‘Temporally’ validate the predictive models using data from the same ambulance service for a later time period (WP2).
(3) Establish a pathway to clinical implementation of the risk prediction tool and maximise usage of RADOSS findings.	g. Complete ‘next steps’ workshops with stakeholders to finalise plans to refine the tool for clinical use and its evaluation (WP3).
	h. Complete a proactive dissemination and knowledge mobilisation strategy (WP3, WP4).

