AA, avoidable attendance; ED, emergency department; KE, Knowledge Exchange; RADOSS, Risk of Adverse Outcomes after a Suspected Seizure; UEC, urgent and emergency care; WP, work package.

Risk prediction tools are specific to clinical scenarios. We are therefore focusing on patients experiencing suspected seizures. Seizures are a topic of interest in their own right but also an ideal exemplar since they are frequently encountered by the service^62 63^ and ‘over-conveyed’.^10^
Table 2 expands on the reasons.

**Table 2 T2:** Reasons why suspected seizures are considered an ideal exemplar

Reason		Detail
1	Frequently seen	Responsible for ~211 000 ‘999’ calls per year in England; 7th most common presentation.^62 63^ Almost all (>97%) receive a face-to-face ambulance response.^103^
2	‘Over-conveyed’	Around 70% of suspected seizure cases are conveyed to ED.^63 103–106^ This is despite national guidelines stating most will not require ED.^47^ Suspected seizures are dramatic and frightening and traditional training emphasises status epilepticus—a rare and life-threating condition. However, most ‘999’ suspected seizures are low risk and persons return to their normal self without intervention.^63^ Most of those presenting have established, treated epilepsy and have experienced an uncomplicated seizure for which they require rest and reassurance.^107^ Seizures currently have the third highest conveyance rate of all presentations.^10^
3	Redeemable cause of avoidable attendance	Clinicians identify suspected seizures as a readily redeemable cause of AAs.^32 33 35 46 108^ At a 2016 International League Against Epilepsy run research priority event, clinicians identified developing a risk tool to support conveyance decisions as a priority.^46^
4	*‘*Alternative care pathways’ available	Alternative care pathways are becoming available for clinicians to use.^109 110^ They could, unlike visits to ED,^111^ prompt improvements in ambulatory care and so address health inequalities.^112^ Their success depends on clinicians identifying people for them.^113^
5	User preference	People with established epilepsy and those with other seizure presentations, such as non-epileptic attack disorder, usually want to avoid ED after an uncomplicated seizure,^114–117^ preferring to recover at home. Unnecessary conveyance to ED puts them at risk of iatrogenic harm and overinvestigation.^118–120^

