##### Sample size

Predictive models for the (1) risk of death/UEC recontact following conveyance, (2) risk of death/UEC recontact following non-conveyance, and (3) risk of an AA following conveyance could be developed. To permit robust testing of at least 40 candidate predictor parameters for each of these models, Riley *et al*’s^72^ formulae using standard parameters indicate: for model (1), a need for 2567 index events, with 103 experiencing the target event; for model (2), a need for 2194 index events, with 308 experiencing the target event; and for model (3), up to 2194 index events, with 461 experiencing the target event. Twelve months of YAS data should be sufficient to satisfy these requirements. Online supplemental file 3 details the reasons why and provides further information on the sample size calculation.

10.1136/bmjopen-2022-069156.supp3Supplementary data

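### The tool offers one patient a risk under conveyance and a risk under non-conveyance, but each model is learned only from patients managed that way, so the comparison is not protected against confounding by indication

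*Protocol article*

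**What the plan says.** **Models.** The Sample size section of WP1a defines the first two models by the management received: (1) "risk of death/UEC recontact following conveyance, (2) risk of death/UEC recontact following non-conveyance". The third is the risk of an avoidable attendance after conveyance. Each has its own requirement. The first is stated as "for model (1), a need for 2567 index events, with 103 experiencing the target event". Model 2 requires 2194 patients and 308 outcomes; model 3 requires at most 2194 patients and 461 outcomes.

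**Method.** The section on derivation of the prediction models specifies multivariable logistic regression. Candidates are picked for relevance to the clinical question, reliable measurement and practicality, then reduced by backward selection at p = 0.10. Control of the conveyance decision is not among the criteria.

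**Use.** The section on combining the models says the tool will give an individual's "risk of death/recontact with the UEC system if managed by non-conveyance; risk of death/recontact with the UEC system if managed by conveyance". The WP1a Purpose section says the same, and the Abstract describes the aim as estimating what a person gains from conveyance and risks without it.

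**Selection.** The Introduction's section on how clinicians decide whom to convey says that need is not the only influence and describes uncertainty and risk aversion. Table 2 says "Around 70% of suspected seizure cases are conveyed to ED".

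**Objective b** in Table 1 is to "Compare the proportions following conveyance and non-conveyance that die and/or recontact the UEC within 3 (and 30) days". It sits under the aim of calculating the risks and benefits of conveyance.

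**The concern.** The stated method is predictive and the stated use is counterfactual. A model fitted in non-conveyed patients estimates the risk of patients with given recorded features whom clinicians left at scene or took elsewhere, or who refused. It estimates the non-conveyance risk of a conveyed patient with the same recorded features only if nothing else that drives conveyance also predicts the outcome. Model 1 has the mirror-image problem. Model 3, the avoidable-attendance model, is likewise learned only from conveyed patients and applied to people who might not be.

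The patients whose management the tool is meant to inform include many of the roughly 70% now conveyed, and for them the non-conveyance figure is extrapolated across the clinician's decision. The strengths and limitations list does not mention this. The Purpose section for the next-steps workshops says that acceptable predictive validity would meet the requirements for use in practice, so the mismatch could pass every planned check.

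**Working it through.** **1. The plan's own figures.** The article does not give the R² used in its sample-size formulae (the supplementary file is not shown). I assume a Cox-Snell R² of 0.15, 40 parameters, a shrinkage target S = 0.90 and optimism in R² of at most 0.05.

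- Shrinkage criterion: n = P / ((S − 1) ln(1 − R²/S)) = 40 / (0.1 × 0.1823) = 2194. This matches models 2 and 3.
- Model 1 at a 4% event rate: maximum R² = 0.2853; S = 0.15 / (0.15 + 0.05 × 0.2853) = 0.9132; n = 40 / ((0.9132 − 1) ln(1 − 0.15/0.9132)) = 2567, with 102.7 events. This matches.

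The sample sizes are sound on that assumption and are not the problem. They do give the implied rates of death or recontact: 103/2567 = 4.0% after conveyance and 308/2194 = 14.0% after non-conveyance. The implied average contrast is −10.0 points.

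**2. What that contrast could hide.** Let U be an unmeasured standard normal factor with log-odds effect g on conveyance and h on the outcome (both assumed). Calibrate to 70% conveyed and to the 4.0% and 14.0% rates, then average each risk over everyone:

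| g | h | Risk if all conveyed | Risk if none conveyed | True contrast (points) |
|---|---|---|---|---|
| −1 | 1 | 5.3% | 9.1% | −3.8 |
| −0.5 | 0.5 | 4.3% | 12.2% | −7.9 |
| 0 | 0.5 or 1 | 4.0% | 14.0% | −10.0 |
| 0.5 | 0.5 | 3.8% | 16.2% | −12.4 |
| 1 | 1 | 3.3% | 22.2% | −18.9 |

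The implied −10.0 holds when U does not drive conveyance. Otherwise it moves either way.

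**3. Whether validation would show it.** I simulated 400,000 patients with 70% conveyed, a 10% outcome rate and no true effect of conveyance. Separate logistic models for the conveyed and the non-conveyed used a measured predictor only. Conveyed-minus-non-conveyed predictions averaged +1.8 points (g = 0.5, h = 0.5), +3.5 (1, 0.5) and +6.1 (1, 1). They were about 0 when U did not drive conveyance, and within 0.3 points of 0 once U was added to both models. Observed/expected within each group was 1.00 throughout. That is so by construction in the fitting data, but a later cohort with the same selection would look the same. The section on temporal validation compares predictions with observed outcomes, and each patient has an outcome under one option only.

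**4. Overlap.** Assume an odds ratio of 3 per SD of a severity factor for conveyance, with 70% conveyed. Then about 20% of conveyed patients have less than a 10% chance of non-conveyance, and model 2 has little data near them. With an odds ratio of 2 the figure is about 5%.

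**The case against.** The strongest reply has four parts.

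- **The predictors are what the clinician sees.** History, observations, clinical features and dispatch data are recorded on scene, and the plan provides for "To permit robust testing of at least 40 candidate predictor parameters for each of these models". Models conditional on these already absorb much of the indication. This stands. Unrecorded judgement, refusal and local factors remain. Excluding refusers is planned only for descriptive proportions.
- **Selection at p = 0.10 does little harm.** With thousands of patients, a dropped variable usually has little association with the outcome given the rest, so it is a minor confounder. This largely stands. The main gap is what is not recorded or never becomes a candidate.
- **The tool is a draft.** The text hedges its claims, presentation is left to the workshops, and an impact evaluation, perhaps a cluster randomised trial, is to follow. This lowers the stakes but does not correct what the outputs are said to mean.
- **Objective b only compares proportions.** As description it is not an error, and a full analysis plan may add standardisation.

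A reader might infer that the tool will understate non-conveyance risk and so reassure falsely. The document does not support a direction. Take a common 14% risk whatever is done, and odds ratios of 3 (conveyance) and 1.5 (outcome) per SD. The observed risk is then 11.1% in the non-conveyed and 15.2% in the conveyed; reversing the selection gives 17.1% and 12.7%. A common 14% also sits badly with the planning rates of 4.0% and 14.0%. A reader might also infer that a risk difference will be displayed. No section says so, although two risks offered for one decision invite the subtraction.

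**Conclusion.** The concern holds as a mismatch between method and claim. The outputs are worded as one person's risk under each option, while the models estimate risk among patients who received that option. The plan describes no weighting, overlap check or forced retention of confounders, and it does not state the limitation. The accurate description is that the comparison is unprotected against confounding by indication; a proven bias is more than the text can show. Its size and direction are unknown, and every illustrative figure above beyond the plan's own rates and the 70% rests on assumed effects of an unmeasured factor. The article itself fixes the model type, selection rule, output wording and validation, so this is not a detail left to an analysis plan. The change should be made, but it does not invalidate the models as predictions within each group.

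**What to change.** 1. **Relabel.** In the WP1a Purpose section and the section on combining the models, describe the outputs as risk among similar patients who were (or were not) conveyed. State that the two risks are not to be read as the effect of conveyance. Add selection into conveyance to the limitations.
2. **Check overlap.** Fit a conveyance propensity model on the recorded dispatch and patient care record variables, report overlap, and flag predictions for patients with little or no support in the relevant group.
3. **Objective b.** Report risks standardised to the face-to-face cohort beside the crude proportions.
4. **If the present wording is kept,** retain recorded determinants of conveyance in models 1 to 3 whatever their p value. Add a sensitivity analysis with inverse-probability weights, stating its loss of precision and its assumption of no unmeasured confounding.

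Items 1 to 3 use data already in the extract and cost a little extra analysis and a more modest claim for the tool. Weighting is not cheap, which is why it is proposed as a sensitivity analysis only. In the scenario with odds ratios of 3 and 1.5, the effective sample in the non-conveyed group falls to about 54%, or 63% to 73% with weights truncated at the 99th or 95th percentile. Applied to the 2194 minimum for model 2, that is 0.54 × 2194 ≈ 1185, or about 1382 to 1602. Truncation also leaves some bias (13.2% to 13.7% against a true 14%), and no weighting removes confounding by what was never recorded.

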#### WP1b: Ke workshops

##### Purpose

Optimise prediction tool development by completing KE workshops with service users, ambulance clinicians and ED clinicians to get views on candidate predictors, the way the outcome measures of death, UEC recontact and AA are defined and risk score presentation.

##### Design

KE workshops will be run online using videoconferencing technology. Wilkins and Cooper^89^ defined KE as a two-way exchange between researchers and research ‘users’ to share ideas, evidence, experiences and skills. It goes beyond telling people things and is a process of listening and interaction, with a goal to generate mutual benefit.

##### Participants

###### Service users

Purposive sample of ~20–30 persons recently receiving ambulance care for a suspected seizure/s and their significant others. Full eligibility is presented in table 4.

Individuals shall be recruited via user groups affiliated with the different conditions (including epilepsy deaths). They shall circulate advertisements directly to their members and within publications.

###### UEC clinicians

Sampling will be purposive, consisting of a group of ~20–30 informed individuals/‘experts’ deemed to have high professional knowledge and clinical experience of the UEC system.

The national ‘Lead Paramedic Group’ will circulate advertisements, with priority being given to ambulance clinicians from the n=6 services that have used Advanced Medical Priority Dispatch System. To recruit ED clinicians, the Royal College of Emergency Medicine Yorkshire and Humber regional board shall circulate advertisements.

##### Procedure

Workshops for service users and ambulance clinicians will run separately. To maximise participation, we anticipate two to three for each. They will be conducted by a qualitative researcher. For those with clinicians, statistician [name] will assist.

Workshops will start with an explanation of the risk tool, aims and a presentation of the potential predictors and proposed outcome measures. A topic guide will direct the conversation. It will be finalised on the basis of the literature,^86 90^ our experience and key uncertainties regarding the tool’s future implementation surfaced by completion of Greenhalgh *et al*’s Non-adoption, Abandonment, Scale-up, Spread and Sustainability Complexity Assessment Tool Long.^91^ The main areas that the workshops intend to cover are shown in table 5. Workshops will last ~60–90 min.

**Table 5 T5:** Topic guide areas that WP1b Knowledge Exchange workshops will explore (emphasis will vary depending on whom the workshop is for)

Area		Detail
1	Potential predictors	Asked for views on potential predictors, including perceived utility, reliability, validity and consistency in measurement.^131^
2	Parameters of outcome measures	Asked whether any routine ED practices could mean seizure cases by default would not satisfy AA definition. Asked about any known differences between EDs and hospitals in how codes for incidents are applied at them that could undermine validity of definition that is based on them. What time frame for death and recontact with UEC would be most supportive for conveyance decisions.
3	Optimal way to present risk scores	Asked whether percentage probability and/or broad risk categories wanted, whether visual aids would help and if estimates of uncertainty around probabilities wanted. Illustrations of options offered. Asked what ‘low’, ‘medium’ or ‘high’ risk of death, UEC recontact or AA would look like to them in percentage terms.
4	Optimal format for tool	Asked how they might want such a tool to be presented in future (eg, web tool, nomogram, graphical score chart), who should have access to it and the extent to which they would want it integrated into existing workflows.^132^

AA, avoidable attendance; ED, emergency department; UEC, urgent and emergency care; WP, work package.

##### Analysis

Data will include field notes and audio recordings. A qualitative researcher, supported by the wider team, will take an inductive and deductive approach to analysis. NVivo will provide a transparent account of the work. Nodes (codes) will be created to mark relevant concepts and topics in the documents. Lower level nodes will be grouped into themes.

### Work package 2

#### WP2: Retrospective cohort study 2

##### Purpose

‘Temporally’ validate WP1a’s predictive models.

The predictions of the WP1a models will be tested on a data set relating to patients cared for by YAS during a 12-month time period different from that used for derivation.

##### Identification, data linkage, data checks and outcome measures

CUREd+ will be searched to identify events as done for WP1a, except the date range will be 1 July 2021 to 30 June 2022 (table 4). Outcome measures and processes used will be the same.

##### Sample size

The validation sample will be similar to that used for derivation. It will thus satisfy the recommendation that validation samples include ≥200 cases experiencing the target events.^92 93^

##### Data management and analysis

###### Describing sample and patient outcomes

Sample contributing data will be described as for WP1a.

###### Comparison with time period used for model derivation

Number of calls for and the characteristics of the patients presenting with suspected seizures during the derivation and validation periods will be compared, as will the proportions conveyed to ED, the proportions whose attendance meets the AA definition and the proportions dying/recontacting the UEC within 3 (and 30) days. Differences will be described and tested for statistical significance.

###### Temporal validation of predictive models

Predictors and regression coefficients from the final internally validated, optimism-adjusted models will be applied to the WP2 data set to predict the target outcomes. The performance of the models will be quantified by comparing predictions with observed outcomes.^94^ Performance will be assessed using measures of discrimination and calibration. Model recalibration will be undertaken if there is systematic underprediction or overprediction.^95^

### Work package 3

#### Next steps’ workshops

##### Purpose

Finalise plans to refine the risk tool for clinical use and its evaluation.

If the developed models are found to make predictions with an acceptable level of validity then we would have satisfied the requirements for the tools use within practice. We would therefore need to finalise its presentations for clinical use and evaluate its impact on clinical practice. To ensure any plans for this are acceptable to stakeholders and address their information needs, ‘Next steps’ workshops will be completed.

##### Design

Two online workshops, each lasting ~3 hours. We shall limit each to approximately eight to nine participants.^96 97^

Workshops will start with a presentation of RADOSS findings and our draft ‘next steps’. To secure stakeholders’ views of these we would use an adapted version of the nominal group technique.^97^

With respect to what evaluation we propose we consider it appropriate to make this judgement nearer the time. A cluster randomised controlled trial would likely be most rigorous. However, various factors can influence and constrain design choice.^55 98^ This includes time frame within which evidence is required and regulations at the time surrounding risk tools.^99^

##### Recruitment

We shall seek representation from:

Service providers (via Association of Ambulance Chief Executives National Ambulance Strategy and Transformation Group).Care guideline providers (via Joint Royal Colleges Ambulance Liaison Committee panel for seizures; National Institute for Health and Care Excellence panel for epilepsy).User groups (including Epilepsy Action, Epilepsy Society, FND Action, SUDEP Action and others).Ambulance research and care quality improvement (via National Ambulance Steering Group; National Ambulance Services Clinical Quality Group).Seizure specialists (via International League Against Epilepsy; Epilepsy Specialists Nurses Association).Commissioners (via National Ambulance Commissioners Network).

Personal invitations will be sent. To maximise attendance, we shall exploit existing relationships our team has. We shall overinvite by ~30%.^100^
Table 4 provides the eligibility criteria.

